### Participants

The study will enroll 240 patients, which fulfill the following items of criteria in this trail.

### Diagnostic criteria

WM diagnostic criteria of diagnosis and treatment guidelines for chronic stable angina pectoris according to the Chinese Society of Cardiology in 2007 [17]TCM diagnostic criteria of Chinese Internal Medicine according to the 11th Five-Year national programmed textbooks together with expert demonstration. The signs and symptoms as follows: chest distress superior and pain inferior, excessive phlegm, shortness of breath, heavy limbs, obesity, attack or aggravation on a rainy day, exhaustion, loss of appetite, loose stool, expectoration, plump tongue and side tooth marks, greasy and glossy coating, slippery pulse

### Inclusion criteria

Diagnosis of CHD with SAP as well as spleen deficiency and phlegm pattern according to WM and TCMAge: male: 45 to 75 years old (including 45 and 75 years old); female: 50 to 75 years old (including 50 and 75 years old)Main coronary artery stenosis between 50% and 75% or branch coronary artery stenosis between 50% and 100% in the previous 3 months as shown on coronary angiogram or coronary computed tomography (CT) examination reportPatients meet Class II to IV of the Canadian Cardiovascular Society (CCS) angina pectoris severity gradeAble to understand and sign a written informed consent

### Exclusion criteria

Pattern differentiation except for spleen deficiency and phlegm patternA history of chest pain caused by the unstable angina pectoris (UAP), hypertrophic cardiomyopathy (HCM), neurosis, post-menopausal pattern, gastric and esophageal reflux disease (GERD), and so onMain coronary artery (right coronary artery (RCA), left main stem (LM), left anterior descending (LAD), left circumflex (LCX)) more than 75% stenosis according to coronary angiogram or coronary CTAcute myocardial infarction in the previous half year or completely revascularization history within a yearSevere heart failure (class IV of heart function), malignant arrhythmia, hypertension higher than 160/100 mmHg within standard anti-hypertensive therapy, other serious system diseases (malignant tumor, gastrointestinal hemorrhage, gastric ulcer, and so on) and function examination of liver and kidney (more than 1.5 times the reference value of aspartate aminotransferase (AST), alanine transaminase (ALT), creatinine (Cr))Mental disorderPregnancy, planned pregnancy and breast-feeding womenChinese medicine granule and iodine allergyGlaucoma patientsA history of another clinical trial in the previous 2 monthsNo consent form signed

### Handling of withdrawal and dropout

Voluntarily withdrawalLoss of follow-upPoor compliance and presence of severe adverse effectsRevealing and uncovering blind in urgencyMisdiagnosisUsing forbidden drugs or treatments in the course of the trialTaking no medication during the trialNo evaluable records after medication

Reasons for withdrawing participants will be recorded in CRFs, and the last data would be included in data analysis.

The whole research plan would be terminated for the following circumstances:Occurrence of serious adverse events related to the research medicationFlawed protocolFunding and management problem due to the sponsorsAdministrative authorities terminate the trial

### Recruitment strategies

We will apply two strategies to recruit participants with angina pectoris. Firstly, we will recruit participants from out-patient clinics and in-patient department in every clinical center. Secondly, potential patients in local communities and out-hospital clinics will be recruited by advertisements in the post, leaflets, TV broadcast and newspapers. The posters will contain brief introductions about the population needed to be involved, the free treatments offered to eligible participants and the contact information of the researcher. Participants will be included if they meet the inclusion criteria and have provided written informed consent indicating that they agree to this trial and join in the trial voluntarily.

### Intervention

#### TCM intervention

Participants randomized to treatment Group 1 will take *Yi-Qi-Jian-Pi* and *Qu-Tan-Hua-Zhuo* granule, which is composed of *HuangQi* (*Astragalus membranaceus*) - 10 g, *DangShen* (*Codonopsis pilosula*) - 10 g, *BaiZhu* (*Atractylodes macrocephala Koidz*) - 10 g, *FuLing* (*Poria cocos Wolf*) - 10 g, *QingBanXia* (*Rhizoma pinelliae Preparata*) - 6 g, *GuaLou* (*Trichosanthes kirilowii Maxim*) - 10 g, *DanShen* (*Salvia miltiorrhiza*) - 10 g, *ZhiGanCao* (*Glycyrrhiza uralensis Fisch*) - 3 g. Those in treatment Group 2 (*Yi-Qi-Jian-Pi* and *Qu-Tan-Hua-Yu* granule) are composed of *DanShen* (*Salvia miltiorrhiza*) - 10 g, *BaiZhu* (*Atractylodes macrocephala Koidz*) - 10 g, *FuLing* (*Poria cocos Wolf*) - 10 g, *ZhiGanCao* (*Glycyrrhiza uralensis Fisch*) - 3 g, *QingBanXia* (*Rhizoma pinelliae Preparata*) - 6 g, *GuaLou* (T*richosanthes kirilowii Maxim*) - 10 g, *TaoReng* (*Prunus persica Batsch*) - 10 g, *HongHua* (*Carthamus tinctorius*) - 6 g. The action and batch number of each herb is summarized in Table 1[7]. The control group is made from *Yi-Qi-Jian-Pi* and *Qu-Tan-Hua-Zhuo* granules (10%) and starch (90%) to achieve the same shape, color, smell, taste, texture package and Lot Number. Patients are instructed to dissolve granules into 100 ml of hot water and to take the solution orally between 30°C to 37°C twice daily for 12 weeks. Each granule is prepared by Jiangyin Tianjiang Pharmaceuticals Co. Ltd, Jiangsu, China according to the standards of Good Manufactory Practice (GMP) [18].

**Table 1 Tab1:** **The action and batch number of each herb**

Ingredients	Lot number	Action
*HuangQi* (*Astragalus membranaceus*)	1302026	TCM: tonifying spleen and protecting defensive *Qi*.
		Pharmaceutical study: 1. Promoting metabolism effect. 2. Diuresis effect. 3. Cardiovascular system protecting effect.
*DangShen* (*Codonopsis pilosula*)	1302095	TCM: tonifying *Qi* of spleen and lung and benefiting blood and body fluid.
		Pharmaceutical study: 1. Adjusting gastrointestinal movement effect. 2. Anti-ulcer effect. 3. Immune-enhancing effect. 4. Anti-aging effect.
*BaiZhu* (*Atractylodes macrocephala Koidz*)	1302011	TCM: tonifying *Qi* of spleen, eliminating dampness and diuresis.
		Pharmaceutical study: 1. Intestinal tube two-way regulation effect. 2. Anti-ulcer effect. 3. Diuresis effect. 4. Strong effect.
*FuLing* (*Poria cocos Wolf*)	1301056	TCM: diuresis, detumescence, tonifying *Qi* of spleen and tranquilization.
		Pharmaceutical study: 1. Diuresis effect. 2. Calming effect. 3. Anti-tumor effect. 4. Anti-diabetic effect. 5. Enhance myocardial contractility.
*QingBanXia* (*Rhizoma pinelliae Preparata*)	1301078	TCM: eliminating dampness, resolving phlegm, controlling vomiting and eliminating stagnation.
		Pharmaceutical study: 1. Vomiting control effect. 2. Anti-tumor effect. 3. Gastric secretion inhibition effect.
*GuaLou* (*Trichosanthes kirilowii Maxim*)	1301157	TCM: clearing heat, reducing phlegm, eliminating stagnation and relaxing bowels.
		Pharmaceutical study: 1. Reducing phlegm effect. 2. Coronary artery dilatation effect. 3. Lipid-lowering effect.
*DanShen* (*Salvia miltiorrhiza*)	1301173	TCM: activating and cooling blood, regulating menstruation, removing stasis and pain.
		Pharmaceutical study: 1. Improving myocardial ischemia effect. 2. Improving microcirculation effect. 3. Hypotensive effect. 4. Platelet aggregation inhibition effect. 5. Liver protection effect. 6. Anti-inflammatory effect.
*ZhiGanCao* (*Glycyrrhiza uralensis Fisch*)	1212045	TCM: tonifying *Qi* of spleen, eliminating phlegm, anti-cough, heat-clearing and detoxifying and reconciling.
		Pharmaceutical study: 1. Anti-arrhythmia effect.2. Anti-ulcer effect.3.Diuresis effect. 4. Analgesia effect. 5. Anti-tussive effect. 6. Eliminating phlegm effect.
*TaoReng* (*Prunus persica Batsch*)	1212013	TCM: activating blood, removing stasis, relaxing bowels and relieving cough and asthma.
		Pharmaceutical study: 1. Cerebral blood flow improving effect. 2. Anti-coagulant effect. 3. Analgesia effect. 4. Anti-allergic effect. 5. Relieving cough and asthma effect.
*HongHua* (*Carthamus tinctorius*)	1212080	TCM: activating blood, regulating menstruation, removing stasis and pain.
		Pharmaceutical study: 1. Improving myocardial ischemia and coronary artery flow effect. 2. Anti-arrhythmia effect. 3. Hypotensive effect. 4. Platelet aggregation inhibition effect. 5. Analgesia and sedation effect. 6. Anti-inflammatory effect.

#### WM conventional intervention

An anti-anginal drug, nitroglycerin, is selected as WM conventional treatment and allowed to be taken at a dose of 0.5 g sub-lingual at at least 5-minute intervals [19].

### Concomitant treatments and forbidden drugs

Patients are not allowed to take any other TCM intervention (acupuncture treatment, angina pectoris plaster, and so on), nitrates except for nitroglycerin, non-dihydropyridine CCBs and lipid-lowering drugsIn the run-in and study period, usage of aspirin, BBs and dihydropyridine CCBs in the previous 4 weeks is allowed to continue and conversion is prohibitedThe dosage, duration and name of any concomitant treatment or medication must be recorded carefully in the CRFs

### Drug management

Seventy-five to 120% of drug usages are eligible for protocol plan. The three groups’ granules will be prepared respectively but uniformly packaged. The package, drug name, function and indication, usage and dosage, storage condition, valid period and name of the manufacturer will be marked and a tag indicating ‘trial use’ will be attached. Drugs must be kept in the appropriate temperature in a dry, shady and cool place. Drug administrators should return unused drugs to estimate participant compliance and note these in the CRFs.

### Outcomes

#### Efficacy outcomes

The primary outcomes include:Frequency of angina pectoris attacksDosage of nitroglycerinBody limited dimension of Seattle Angina Questionnaire (SAQ)

The secondary outcomes include:SAQ except for the body limited dimensionTCM pattern questionnaireThe duration of angina pectorisAngina pain severity

#### Therapeutic mechanism outcomes

Blood serum metabolites; total cholesterol (TC); triglycerides (TG); low-density lipoprotein (LDL); high-density lipoprotein (HDL); ox-LDL; hypersensitive C reactive protein; homocysteine; glucagon like peptide-1; angiotonin II; HMG-COA reductase; adherence factor PS; scavenger receptor A; scavenger receptor B; chemokine MCP-1; adherence factor vascular cell adhesion protein (VCAM)-1; 5-HT; vasointestinal peptide (VIP); ghrelin; norepinephrine (NE); acetylcholine (Ach); mtDNA copy number; MicroRNA155; MicroRNA 33; MicroRNA 126; MicroRNA 125; MicroRNA 221; MicroRNA 222.

#### Safety outcomes

For the sake of participant safety, the following biological indicators will be monitored and watched throughout the trial: blood routine, liver function (AST, ALT), renal function (BUN, Cr), and electrocardiograph (ECG). Adverse events are defined as any unexpected or uncomfortable signs, symptoms, or diseases. Once adverse events happen during the treatment and follow-up period, all the details should be documented in the CRF form and reported to the ethics committee immediately so that they can make a decision about whether the patient should withdraw from the trial.

#### Endpoint outcomes

Death incident: cardiovascular death, cerebrovascular death, sudden death, other cause of death.

Cardiovascular incident: unstable angina pectoris hospitalization, acute myocardial infarction, malignant arrhythmia, cardiac shock, revascularization and other cardiovascular incident.

Non-cardiovascular incident: stroke, pulmonary embolism, peripheral vessel, tumor, other non-cardiovascular incident.

All three groups will undergo a twelve-week treatment and two-week follow-up. Four visits in sum will be scheduled for each subject: one visit each in week 0, week 4, week 12 and week 14. The CRFs contains a range of information and this will be completed by the corresponding researchers at each center. Trial coordinators and therapists at each center will record above endpoint outcome and the details of these events throughout the treatment and follow-up period. Outcomes to be measured and the time points of data collection can be found in Additional file 1: Table S1.

### Quality control

Quality control will be conducted by rigorous monitoring throughout the trial. All staff who enroll participants, assessors who collect data and management who distribute drugs must attend training to make sure all practices at each hospital are generalized and standardized according to the standard operating procedures (SOP). Physicians must pass the required training test to understand the purpose and content of the trial, intervention strategies and any adverse events observation. To guarantee compliance, researchers must remind the participants of the regular visits ahead of 2 or 3 days.

### Sample size calculation

According to the response rates of treatment, Group 1 and placebo were 88.5% and 60%, respectively; 37 patients of each group was estimated as sufficient to achieve 80% power in detecting treatment differences, based on two-sided Chi-square test without continuity correction at a significance level of 0.05 (α = 0.05; 1-β = 0.80). In the same way, assuming the clinical effective rates of Group 2 and placebo were 82.5% and 60%, respectively and 64 patients of each group was estimated as sufficient to achieve 80% power. Meanwhile, taking into account a dropout of 15%, we concluded that a total of 240 patients with 80 for each group would need to be recruited to ensure statistically significant results.

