### Statistical analysis

The statistical analysis will be conducted by a statistician of the Beijing Bozhiyin Science and Technology Co. Ltd, China. They are blinded to the whole trial and using Statistical Analysis System (SAS, Cary, NC, USA) version 9.2 and Statistic Package for Social Science (SPSS, Chicago, IL, USA) version 17.0 software packages. All mechanism, efficacy and safety analyses will be strictly conducted according to the intention-to-treat (ITT) principle and the full analysis set (FAS) population, the per-protocol set (PPS) population and the safety set (SS) population. Missing values will be replaced by the last observation carried forward (LOCF) method.

The statistical significance is defined as a two-sided *P*-value of <0.05 and 95% confidence interval. For descriptive statistics, continuous variables will be described as numerous, mean ± standard deviation, median, Q1 to Q3 and mini-maxi and dichotomous data will be reported as frequency and percentage. Baseline differences among the groups will be assessed with the use of Student’s *t*-test for normally distributed continuous variables and the non-parametric Mann-Whitney *U*-test for non-normally distributed variables. Comparisons between groups will be conducted by using an analysis of covariance (ANCOVA) with baseline as covariate. For efficacy analysis, changes from baseline to endpoint of treatment in scores will be tested with repeated measure analysis of variance (ANOVA). Within group differences will be assessed with paired *t*-test for normally distributed data and Wilcoxon signed-rank test for non-normally distributed data. Mechanism will be assessed between mechanism index and primary outcomes by ANCOVA and regression analysis. Safety will be assessed by participant compliance and adverse events. The endpoint events will be listed by detailed account.

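### The 240-patient sample size and its 80% power are calculated for an undefined response rate that the article neither lists as an outcome nor links to a test, so the stated power applies to none of the three primary outcomes

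*Protocol article*

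**What the plan says.** **Sizing.** The protocol article's Sample size calculation rests on two comparisons of proportions. For the first it says "According to the response rates of treatment, Group 1 and placebo were 88.5% and 60%, respectively", and that "37 patients of each group was estimated as sufficient to achieve 80% power in detecting treatment differences". The method is "based on two-sided Chi-square test without continuity correction at a significance level of 0.05" ("α = 0.05; 1-β = 0.80"). The second proceeds in the same way, "assuming the clinical effective rates of Group 2 and placebo were 82.5% and 60%, respectively", and concludes that "64 patients of each group was estimated as sufficient to achieve 80% power". After a 15% dropout allowance the total is set at 240, 80 per group, and the section presents this number as assuring statistically significant results. The quantity is called a response rate in one sentence and a clinical effective rate in the next. Neither term is defined.

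**Outcomes.** Under Efficacy outcomes: "The primary outcomes include:Frequency of angina pectoris attacksDosage of nitroglycerinBody limited dimension of Seattle Angina Questionnaire (SAQ". The Abstract lists the same three. The secondary outcomes are the other SAQ dimensions, the TCM pattern questionnaire, angina duration and pain severity. The therapeutic mechanism, safety and endpoint sections list biomarkers, laboratory and ECG monitoring, adverse events and clinical events. No response or effective rate appears in any of these lists.

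**Analysis.** Under Statistical analysis: "Comparisons between groups will be conducted by using an analysis of covariance (ANCOVA) with baseline as covariate". Changes in scores from baseline to the end of treatment go to a repeated-measures ANOVA. No test of proportions between groups is named. Dichotomous data are mentioned only in the sentence on descriptive summaries.

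**The concern.** A sample size calculation supports a power claim only for the variable, effect and test that went into it. Here the three parts do not meet. The sizing uses a proportion and a chi-square test, the primary outcomes are a count, an amount and a score, and the planned comparisons are for continuous data. The article gives no bridge between them, such as a cut-off that turns a primary outcome into a response.

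Two things are at stake. First, readers will take 80% power as a property of the primary analysis, and may lean on it when judging a negative result. The document gives no basis for that. Second, an effective rate defined after the data are seen would have a freely chosen cut-off and yet would look prespecified, because the sample size paragraph mentions it.

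**Working it through.** **Inputs from the document (Sample size calculation; Randomization and allocation concealment).** Rates 0.885 and 0.825 against 0.60; two-sided α 0.05 (z = 1.960); power 0.80 (z = 0.8416); allocation 1:1:1; no continuity correction; dropout 15%; 80 per group.

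**Step 1: reproduce the stated sizes.** Pooled two-proportion formula, with p̄ the mean of the two rates:

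n = [1.960·√(2p̄(1−p̄)) + 0.8416·√(p₁(1−p₁) + p₂(1−p₂))]² / (p₁−p₂)²

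- Group 1: p̄ = 0.7425, so n = [1.960·√0.3824 + 0.8416·√0.3418]² / 0.285² = 35.7, that is 36 (stated 37; power at 37 is 81.4%).
- Group 2: p̄ = 0.7125, so n = [1.960·√0.4097 + 0.8416·√0.3844]² / 0.225² = 62.3, that is 63 (stated 64; power at 64 is 81.1%).

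The stated figures are within one patient per arm. Other versions fit worse: 43 and 71 with continuity correction, 34 and 60 with unpooled variance, 29 and 49 one-sided.

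**Step 2: dropout.** 64/0.85 = 75.3, that is 76 per group or 228 in total, rounded up to 80 and 240. Conversely, 80 × 0.85 = 68 evaluable per group. On the rate itself, 68 per group gives power of 97.4% (Group 1) and 83.4% (Group 2). The arithmetic is in order, so the fault lies in the endpoint.

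**Step 3: can the power be carried over to the primary outcomes?** That needs a mean difference and SD, or event rates, for attack frequency, nitroglycerin dosage or the SAQ dimension. The document gives none, so neither a required N nor a power can be calculated for them.

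**Step 4: illustration only.** Assume one pairwise comparison, two-sided 0.05, 80% power and an approximately normal scale. The detectable standardised difference is d = (1.960 + 0.8416)·√(2/n) = 2.8016·√(2/n). For ANCOVA, multiply by √(1−ρ²), where ρ is an assumed correlation with baseline.

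| Analysed per arm | Unadjusted | ANCOVA, ρ = 0.5 |
|---|---|---|
| 68 (80 less 15%) | 0.48 | 0.42 |
| 80 (full analysis set with LOCF) | 0.44 | 0.38 |

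At 68 per arm, ρ = 0.3 gives 0.480 × √0.91 = 0.46 and ρ = 0.7 gives 0.480 × √0.51 = 0.34.

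Unadjusted power at 68 per arm depends almost entirely on the difference assumed: 21% at d = 0.2, 42% at 0.3, 65% at 0.4, 83% at 0.5 and 94% at 0.6. No passage favours one of these values over another.

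**The case against.** **The rate may be tested after all.** A journal article that names no chi-square test does not exclude one. A statistical analysis plan may assign tests by variable, and Additional file 1: Table S1, which holds the outcome schedule, is not shown. This stands as a limit on wording. A reader might infer that the rate will never be tested; the article does not support that. What it shows is that the rate is tied to no outcome it lists and no test it names. The point is still more than missing detail, because sizing variable, outcomes and main tests are all stated and do not agree.

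**The rate may be a dichotomy of a primary outcome.** This is possible. If it were a normally distributed outcome cut at a threshold, the assumed rates would imply d = 0.935 − 0.253 = 0.68 (82.5% against 60%) and 1.200 − 0.253 = 0.95 (88.5% against 60%), and 68 per arm would give power of about 98% and above 99%. The assumption cannot be checked, since no cut-off is given. It does show that low power is not established.

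**The analysed number may be nearer 80 than 68.** Statistical analysis plans intention-to-treat and full-analysis-set analyses with LOCF, and the section on withdrawal and dropout keeps the last data of withdrawn participants. This stands, and both numbers are shown above.

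**A standardised difference suits a count or an amount poorly.** This also stands. The table is an order of magnitude and should not be copied into the protocol for attack frequency.

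**A null result can still be interpreted.** Correct. The section plans 95% confidence intervals, and they stay informative whatever was assumed at the design stage. What is lost is the right to cite the planned power in support of a negative conclusion.

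**Conclusion.** The point holds as a mismatch between stated elements. The 80% power in the Sample size calculation belongs to an undefined response or clinical effective rate under a chi-square test, and it applies to none of the three primary outcomes. The assurance that 240 patients will yield significant results therefore has no stated support for those outcomes.

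The effect on actual power is unknown. A reader might infer that the trial is underpowered; the documents do not support this, because they give no SD, rate or target difference for any primary outcome, and results under assumed values range from poor to ample. The detectable differences of 0.38 to 0.48 rest on a normal approximation, a single pairwise comparison at 0.05, either 68 or 80 analysed per arm, and an assumed baseline correlation of 0 or 0.5.

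The conclusion about listed outcomes and named tests is limited to the article text.

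**What to change.** Settle the matter before unblinding, with N left at 240, by one of two routes.

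(a) If the rate is what the trial was meant to test, define it using the cut-off already in the source from which the 88.5%, 82.5% and 60% were taken. List it among the outcomes, state its rank relative to the three primary outcomes, and name the chi-square or logistic test that will compare it between groups. A cut-off newly chosen at this stage would not serve.

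(b) Otherwise, withdraw the statement that 240 patients give 80% power and assure significance. State instead what 240 patients give for each listed primary outcome under the planned ANCOVA, with sourced SDs or rates, and with count-based inputs for attack frequency.

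The documents give no ground for preferring one of the three primary outcomes over the others, and neither route requires it.

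The cost is a change of wording and the work of finding sourced inputs; no extra patients are needed. Because Trial status reports that recruitment is ongoing, the change should be dated and recorded as an amendment. The downside is that the stated power may become less favourable.
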